## Abstract

**Background:**

Most young people with type 1 diabetes (T1D) fail to achieve internationally recommended glycemic targets despite recent advances in diabetes technology and education. There is significant variability in management practices and glycemic outcomes across diabetes services, and the need for a more unified approach has been recognized. The Success with Individualized Insulin Management (SWIIM) program, developed at John Hunter Children’s Hospital (JHCH) in New South Wales (NSW), Australia, has demonstrated glycemic outcomes among the best reported nationally for pediatric diabetes. However, its feasibility and effectiveness have not been tested.

**Objective:**

This study aimed to evaluate the implementation of SWIIM across metropolitan and non-metropolitan healthcare settings in NSW, assessing its feasibility, cost-effectiveness, and impact on clinical outcomes.

**Methods:**

A pre–post-implementation study will be conducted in three hospitals: two non-metropolitan sites in the Mid-North Coast Local Health District (MNCLHD) and one metropolitan site in the Nepean Blue Mountains Local Health District (NBMLHD). An education program will be delivered to clinicians with written resources and clinical support. All children and young people aged 0–18 years with T1D receiving care at these sites receive SWIIM for diabetes management. Data will be collected over an 18-month implementation period with retrospective pre-intervention data for comparison. The primary outcome was the change in HbA1c levels over the implementation period. Secondary outcomes included continuous glucose monitoring (CGM) metrics, insulin therapy modality, adherence to complication screening, hospitalization rates, and program feasibility indicators. Acceptability will be assessed using validated patient- and clinician-reported measures. A cost-effectiveness analysis will be performed to determine the financial impact of implementing the SWIIM over standard care.

**Discussion:**

This study aims to evaluate the implementation of a structured, evidence-based pediatric diabetes management program in diverse Australian health service contexts. If successful, SWIIM could provide a scalable and sustainable model of care that improves outcomes and healthcare delivery for pediatric T1D.

## Background

Type 1 diabetes (T1D) can result in significant morbidity and mortality if not optimally managed. The Diabetes Control and Complication Trial (DCCT) of young people and adults demonstrated that over a 30 year follow up period intensive insulin management coupled with comprehensive diabetes education reduced the rate of diabetes-related complications by 30%–49% and lowered mortality by 33% (1). The widespread uptake of diabetes technologies (continuous glucose monitoring [CGM] and insulin pump therapy [IPT]) and the availability of automated insulin pump systems over the 20 years since the initial DCCT publication have been linked to improved glycemic control and improved patient and carer quality of life (2, 3). Consequently, various guidelines, including those of the International Society for Pediatric and Adolescent Diabetes (ISPAD) (4) and the National Institute for Health and Care Excellence (NICE) (5), recommend an HbA1c target of 6.5% (48 mmol/mol) where there is access to advanced diabetes technologies to minimize the risk of diabetes-related complications.

Despite these advances and guidelines, most children and young people with T1D worldwide do not meet the recommended target. The T1D Exchange reported that only 17% of youth in their large database met the target of 7.5% (58 mmol/mol) between 2016 and 2018 (6). In 2022, it was reported that only 12.5% of adolescents and young adults with T1D in Australia achieved the recommended HbA1c target of 7.0% (7). Importantly, there is significant variability in outcomes between diabetes services, which can be attributed to various patient-, clinician-, and system-level factors (8, 9). There is a need for improved evidence-based management strategies that enable young people and their families to achieve these recommendations.

The Success with Individualized Insulin Management (SWIIM) Program is a pediatric diabetes management program encompassing inpatient and outpatient education and management delivered by a multidisciplinary team at the John Hunter Children’s Hospital (JHCH), a tertiary center in NSW, Australia, since 2004. Using the SWIIM program, the JHCH consistently achieves some of the best outcomes for pediatric T1D in Australia and globally (10). The outcomes of the SWIIM and details of the program have been published (11–13). The effectiveness and feasibility of implementing of SWIIM at other sites have not been tested in a research environment.

Approximately 27% of the Australian population lives in non-metropolitan areas (14) and faces unique geographical, financial, and health system challenges, resulting in poorer health outcomes than those living in metropolitan areas. The Modified Monash Model (15) (**Supplementary Table 1**) classifies areas from metropolitan to remote based on the population size and geographic remoteness. In non-metropolitan areas, the lack of consistent reporting of outcome data means that the true burden of T1D is not fully understood (16). The limited existing literature suggests that people with T1D in non-metropolitan areas are less likely to meet glycemic targets (16, 17), have less access to specialist healthcare resources (18), and experience higher psychological burden (19) than their metropolitan counterparts. Additionally, there is no standardized model of care for delivering diabetes care tailored to the non-metropolitan healthcare delivery context.

When access to specialist care is available through outreach clinics, young people with diabetes report satisfaction with their healthcare (20). However, this model can result in fragmented access to services, and when specialist care is unavailable, there is increased reliance on primary healthcare providers who may not have extensive experience with T1D (20).With rapidly advancing technology becoming part of routine T1D care, there is potential for widening health inequity due to lack of access to specialized knowledge and education. A model of care that utilizes existing resources, upskills local providers, and empowers families living with T1D may be a more sustainable model for delivering recommended care and resulting in improved health equity across non-metropolitan areas. Such a model aligns with the proposed service delivery strategy of the Australian National Rural Health Alliance to upskill and support local clinicians and reduce reliance on fly-in–fly-out models (21).

The education and empowerment of children and young people with diabetes and their families are vital for effective diabetes treatment (22). The ISPAD recommends that structured, individualized education be delivered by a multidisciplinary team and provides guidance on the key aspects of diabetes education (23). The complexity of day-to-day management and the paucity of evidence-based structured diabetes management programs for the pediatric population means that there is significant diversity in the educational practices delivered by diabetes teams globally (24).

This study aimed to determine whether the implementation of SWIIM results in improved diabetes outcomes and patient and clinician satisfaction over standard care in metropolitan and non-metropolitan healthcare settings. Ethics approval was granted by the Hunter New England Health Research Ethics Committee (approval no. 2022/ETH01116).

## Methods

### Study design and setting

A pre-post implementation study will be conducted at three sites providing outpatient and inpatient pediatric diabetes care in New South Wales (NSW), Australia. Two of the sites (Port Macquarie and Coffs Harbour) are level 5 public hospitals in the Mid-North Coast Local Health District (MNCLHD). The third center (Nepean) was a level 6 tertiary public hospital in the metropolitan Nepean Blue Mountains Local Health District (NBMLHD). The characteristics of the health districts in comparison to the JHCH, where SWIIM was developed, are presented in **Supplementary Table 2**. The sites were selected to allow analysis of SWIIM implementation in a variety of settings with differing staffing levels and diabetes-specific expertise across metropolitan and non-metropolitan populations.

The implementation of a practice change intervention will occur over an 18-month period (**Supplementary F****igure 1**), during which eligible patients will be recruited. The intervention will be delivered simultaneously across the three sites. Given that the intervention occurs at a site-wide level, a within-center randomization protocol would not be possible. Pre-intervention (usual care) data will be retrospectively obtained from the electronic medical records of recruited the patients. Patients who are newly diagnosed during the study period or for whom retrospective data are not available will also be included for statistical analysis at the available time points (see *Statistical analysis*).

#### Patient involvement

Patients attending the JHCH pediatric diabetes clinic were heavily involved in the development of SWIIM since its inception in 2004. Patients were not directly involved in the study design or methodology; however, Aboriginal community feedback from the study sites was sought in the design of the research project.

### Participants and recruitment

#### Pediatric diabetes services

In the MNCLHD, where there are 110 young people with type 1 diabetes, the average HbA1c level is 8.6%. Each of the two sites is served by a general pediatrician, diabetes educator, and dietitian. The diabetes educator and dietitian were also shared with adult diabetes services. The inpatient ward at each site is a mixed pediatric unit staffed by pediatric trained nurses, and there is access to social workers and Aboriginal health officers that service the entire hospital. Pediatric endocrinologists from JHCH provide six monthly outreach clinics to MNCLHD, an arrangement that began 24 months prior to the study commencement. Patients are reviewed in outpatient clinics three to four times per year.

In NBMLHD, where there are 220 young people with T1D, the average HbA1c level is 8.1%. The team comprises pediatric endocrinologists, dietitians, diabetes educators, and social workers. Patients are reviewed in outpatient clinics three to four times per year. The inpatient ward is a mixed pediatric unit staffed by pediatric trained nurses and there is access to Aboriginal health officers.

#### Clinicians

The practice change intervention will be delivered to all clinicians providing care for young people with type 1 diabetes at the three sites: diabetes nurse educators, diabetes dietitians, social workers, ward nurses and dietitians, Aboriginal health workers, medical practitioners (pediatricians/endocrinologists, fellows, registrars, resident medical officers), and students. At the completion of the intervention period, clinicians who attended SWIIM education sessions and provided a contact email address will be invited by email to complete the digital clinician satisfaction survey and participate in a semi-structured interview.

#### Young people with type 1 diabetes

All young people aged 0–18 years with an existing diagnosis of type 1 diabetes or a new diagnosis within the study period in the catchment area of the three study sites will receive SWIIM education and management from local teams as part of routine care. Patients and their accompanying carers will be recruited by local clinicians for data collection as part of the study at their first face-to-face contact point during the intervention period. Written consent will be obtained to complete the satisfaction questionnaires and collect clinical data as part of the study. Patients and carers will have the opportunity to decline participation in the study or withdraw their consent at any point. Participation in the study did not alter the patient’s receipt of SWIIM as part of clinical care given the practice-wide intervention.

### Intervention

#### SWIIM model of care

The Success with Individualized Insulin Management (SWIIM) Program is an award-winning, patient-centered, multi-component model of care developed and implemented at the JHCH since 2004 (11). It comprises the management of type 1 diabetes from diagnosis to transition to adult services and is delivered by a multidisciplinary team. Patient management under SWIIM begins with inpatient admission for the initiation of ongoing flexible insulin dosing and diabetes education. SWIIM management principles were incorporated into all outpatient reviews. The SWIIM management principles include:

Teamwork: The team will operate using the principles of Collaboration, Openness, Respect and Empowerment. All members of the diabetes team provided consistent messaging to families. Team members collaborate to reinforce the messages of other team members.Standardized clinic targets for glycemic metrics: Standardized targets for glucose levels (GLs), Hba1c and CGM metrics will be agreed upon and communicated by the team. A target GL of 3.5 mmol/L–8.0 mmol/L is recommended for all ages at all times of the day. An HbA1c target of 6.5% is recommended for all ages.Insulin dosing and adjustment: Insulin is administered 15 min before four meals per day (breakfast, lunch, afternoon tea, and dinner) for all ages for MDI use and before all meals for IPT. Individualized insulin dosing calculations were provided for each meal and adjusted at regular intervals.Structured eating and mealtime routine: A structured approach to eating, informed by the Australian Dietary Guidelines 2013 (25) is advised, with three main meals and two snack times per day. Individualized recommendations for the maximum/minimum carbohydrate amounts per meal and snack were provided. Additional snacking between meals and at bedtime is discouraged.Exercise management: Physical activity is recommended based on the Australian physical activity and exercise guidelines (26), and advice for insulin adjustment for exercise is provided.Carbohydrate counting from diagnosis: Carbohydrate counting is initiated with the first dose of insulin at the diagnosis of T1D. Education on carbohydrate counting is provided in accordance with ISPAD guidelines during the initial inpatient admission (23).Supervision of insulin administration: Carers and educators are encouraged to supervise all doses of insulin.Continuous glucose monitoring: CGM is commenced as soon as possible after diagnosis, and all young people are encouraged to use CGM for at least 90% of the time. Families were educated on CGM interpretation in accordance with the ISPAD guidelines (27) and encouraged to review CGM patterns at regular intervals.Family education and empowerment: From initial admission, families receive education in decision-making regarding insulin adjustment, management of exercise, and sick days. Following discharge from the hospital, daily phone contact with educators was maintained to provide further directed training on insulin adjustment based on GLs. Written sick-day plans provide guidance on insulin adjustment and when to seek medical attention.Identification and management of psychological comorbidities: Communication within families is encouraged to maintain good psychological health. If families express concerns about psychological health, a brief intervention with a social worker is arranged, and/or a recommendation for GP review is made for consideration of mental health intervention.

The model of care will be delivered to families with the following components:

Inpatient insulin initiation and education program for newly diagnosed type 1 diabetes: A standardized education package for newly diagnosed type 1 diabetes was delivered by diabetes nurse educators, dietitians, and social workers over a 5–7-day inpatient admission. Medical officers initiate and adjust subcutaneous insulin doses. Receipt of education is verified by an education checklist completed by families and educators and a carbohydrate counting quiz performed prior to discharge. Following discharge, daily phone follow-ups for ongoing education and insulin dose adjustment were provided for 7–10 days.Three monthly outpatient follow-ups: Young people will be reviewed by a diabetes educator and dietitian 2 weeks after diagnosis. Thereafter, young people are reviewed in outpatient clinics four times per year by physicians. At least one review each with the diabetes educator, dietitian, and social worker (where available) is arranged annually. During outpatient appointments, insulin doses are titrated, and SWIIM management principles are communicated to patients and families.School education: Schools, preschools, and daycare centers that each patient attended received educational session delivered by a diabetes educator. An individualized school plan was provided for each patient. Schools can contact diabetes educators by phone during business hours. The school visit is repeated if there is a change in therapy or the child attends a new school.Written resources: A printed 10 Essential Habits document summarizing key SWIIM principles will be provided to all families from the initial inpatient admission or at the first outpatient clinic review during implementation. Additional printed resources will be provided to the local teams and distributed by clinicians at their discretion, including written and pictorial dietary guidance, insulin dosing guidance, and exercise management strategies. Pro forma for individualized written plans for schools, day care centers, and camps will be provided to local teams.Insulin pump therapy initiation: Patients and families who wish to commence insulin pump therapy will be enrolled in an outpatient education program comprising a 1-hour group pre-pump education workshop with a diabetes educator and dietitian, followed by a 1-hour face-to-face session with the educator and pump company representative for commencement of the pump. Daily phone follow-up was provided for the week after pump initiation to adjust insulin doses until euglycemia was achieved. Insulin pump therapy is not commenced until at least 3–6 months after diagnosis to allow for maximal familiarization with MDI administration.Stabilization admissions: At the team’s discretion, elective admissions to the hospital are utilized to repeat the inpatient education program and adjust insulin doses.Hospital staff education: A hospital procedure document on insulin administration, hypoglycemia management, mealtime routine, and glycemic target is available in hard copy on pediatric wards and on the hospital intranet. Thirty-minute face-to-face training sessions with ward nursing staff are delivered by diabetes educators or dietitians at 3–4 monthly intervals, or as requested by ward staff. Dietitians oversee carbohydrate counting of hospital meals to allow for accurate insulin dosing in hospitals. A written dietary guide, individualized to the child’s age, was provided to the nursing staff to inform them of the appropriate carbohydrate quantities for each meal and snack.

### Implementation intervention

A multi-component clinical practice change intervention will be implemented at each site over an 18-month phase to support embedding SWIIM into the participating sites. Clinicians will be supported to provide the SWIIM program as part of the routine inpatient and outpatient management of T1D in children and adolescents. Through collaborative review with JHCH and implementation site clinicians, aspects of both inpatient and outpatient delivery of SWIIM may be adjusted to suit the local context and the available resources. Deviations from the standard SWIIM implementation will be reported in the final analysis.

#### Implementation intervention strategy development

The following strategies were undertaken to develop implementation strategies:

Collaborative project development meetings were held with key stakeholders at the participating sites to identify barriers and enablers to the implementation of the SWIIM program.The priority barriers were mapped to the Theoretical Domains Framework (TDF) techniques for behavior change (28).Consultation with Aboriginal health workers at the participating sites was undertaken to ensure that the implementation was culturally appropriate.The final refinement of the implementation strategies was undertaken following consultation with key clinicians and managers across the participating health districts.

#### Implementation intervention strategies

The implementation strategies used to support the introduction of SWIIM within the three study sites are presented in **Supplementary Table 3**. The TDF domains that formed the basis for each strategy, as well as the barriers that the strategy intended to address, are listed with a description of each strategy.

### Data collection procedures and measures

#### Patient characteristics

At recruitment (which occurs during the intervention period), the research staff will extract demographic data from the electronic medical records, including age, sex, duration of diabetes, and Aboriginal/Torres Strait Islander status. Area-level socioeconomic status will be assigned using residential postcodes mapped to SEIFA’s Index of Relative Socio-economic Disadvantage (reported in quintiles) (29).

#### Primary outcome measures

The primary outcome was glycemic control, measured as HbA1c (%) for each patient, obtained from the EMR. Analyses will be conducted on individual-level data, with modelled effects expressed as changes in the monthly clinic mean HbA1c from the 6-month pre-implementation period to the end of the 18-month implementation period (**Supplementary F****igure 1**). Additional primary outcome data from MNCLHD sites will be collected for the 12 months prior to the commencement of JHCH pediatric endocrinologist outreach clinics through to the commencement of implementation.

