#### Secondary clinical outcome measures

Additional patient clinical outcome data were obtained from the electronic medical records at the MNCLHD and NBMLHD sites throughout the pre-intervention and implementation periods. The collected data included:

Body mass index (BMI) and BMI standard deviation.Method of insulin administration (fixed insulin dose regimes, flexible multiple daily injections, insulin pump therapy).CGM metrics: Sensor wear time, time in range (3.9 mmol/L–10.0 mmol/L, 70 mg/dL–180 mg/dL), time in tight range (3.9 mmol/L–7.8 mmol/L), time below range (<3.9 mmol/L, <70 mg/dL), time in hypoglycemia, level 2 (<3.0 mmol/L, <54 mg/dL), time above range (>10 mmol/L, >180 mg/dL), and time in hyperglycemia, level 2 (>13.9 mmol/L, >250 mg/dL).Adherence to international recommendations for diabetes-related complication screening (30) in the 12 months preceding implementation to study completion.Number of hospitalizations for diabetes in the 12 months preceding implementation to study completion (not including initial diagnosis).

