### Statistical analysis

The primary analysis will evaluate the change in glycemic control, measured by HbA1c at the individual level, from the 6-month pre-implementation baseline period to the end of the 18-month implementation period. Data will be modeled at the patient level, with clinic means over time used as the primary summary measure for interpretation.

A linear mixed-effects segmented regression model will be fitted, with fixed effects for time pre-intervention (monthly index), period (0 = per-implementation, 1 = implementation), time post intervention (which is zero during pre-intervention months and increments monthly thereafter), site, and patient-level covariates: age, sex, diabetes duration, Aboriginal and Torres Strait Islander status, and SEIFA quintile. The model will include a random intercept for patients to account for potential repeated measurements, and an autoregressive (AR(1)) correlation structure will be examined to account for within-patient autocorrelation over time. Effects will be expressed as (i) immediate level change and (ii) change in monthly slope, both relative to the counterfactual pre-implementation trends. Robust (sandwich) standard errors were calculated. Distributional and other modelling assumptions will be assessed by inspecting residual plots, with transformations or different distributional families (e.g., proportional odds logistic models) considered. Secondary outcomes with repeated measures will be assessed using a similar model with an appropriate distributional family dependent on the outcome type.

To assess the impact of medical outreach clinics in the MNCLHD prior to the study onset, an additional comparison of the primary outcome will be made from the commencement of medical outreach clinics to the commencement of the implementation period.

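### The primary segmented model projects a 6-month pre-trend over 18 months with no seasonal term, so any seasonal variation in HbA1c can bias the declared level and slope changes in either direction

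*Protocol article*

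**What the plan says.** The window is given twice. Under Primary outcome measures, effects are "changes in the monthly clinic mean HbA1c from the 6-month pre-implementation period to the end of the 18-month implementation period". Under Statistical analysis, change is evaluated "from the 6-month pre-implementation baseline period to the end of the 18-month implementation period".

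The model is a linear mixed-effects segmented regression "with fixed effects for time pre-intervention (monthly index), period (0 = per-implementation, 1 = implementation), time post intervention". The other fixed effects are site, age, sex, diabetes duration, Aboriginal and Torres Strait Islander status and SEIFA quintile. No calendar-month, seasonal or harmonic term is listed. An AR(1) structure is to be examined, and robust standard errors are used. On the estimands: "Effects will be expressed as (i) immediate level change and (ii) change in monthly slope, both relative to the counterfactual pre-implementation trends".

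Study design and setting says delivery starts at the same time at all three sites. The Discussion acknowledges that there is no contemporaneous control group.

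Other data reach back further. For the MNCLHD sites, HbA1c "will be collected for the 12 months prior to the commencement of JHCH pediatric endocrinologist outreach clinics through to the commencement of implementation", and outreach is "an arrangement that began 24 months prior to the study commencement". The Statistical analysis section assigns the outreach period to a separate comparison. Two secondary outcomes also look back further: "Number of hospitalizations for diabetes in the 12 months preceding implementation to study completion", and likewise complication screening.

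**The concern.** A straight line fitted through half an annual cycle cannot separate season from trend. If HbA1c happens to fall over those six months for seasonal reasons, the model takes the fall as the usual-care trajectory and carries it forward for 18 months, three times the span over which it was observed. The seasonal rebound then looks like harm from SWIIM. If HbA1c happens to rise, the rebound looks like benefit.

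Nothing else in the design separates the two. A common start date puts every site at the same point of the cycle, and there is no control series to subtract. AR(1) errors and sandwich standard errors concern variance and leave a shared seasonal mean pattern in place. More patients would only narrow the interval around a biased value. Both declared primary effects use this projected line as their reference.

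**Working it through.** **Plan's own figure.** The protocol gives no figure for seasonality, so there is none to reproduce. The only benchmark is the 1-point HbA1c change in the sample-size section.

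**Inputs from the protocol.** 6 pre-months; 18 post-months; time terms as listed (intercept, monthly time, period, time since implementation); no seasonal term; common start; no control.

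**Assumption, not in the protocol.** Mean HbA1c follows A·cos(2π(t − φ)/12), with amplitude A in percentage points (peak to trough 2A) and phase φ set by when the cycle peaks relative to the start. There is no true effect.

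**Step 1: bias per unit amplitude.** With X the segmented design on monthly means, the expected coefficients are (X'X)⁻¹X'y, where y is the cosine alone. The table gives the largest absolute value over all phases. The month-18 gap is level change + 18 × slope change.

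| Pre-months | Level change | Slope change per month | Month-18 gap |
|---|---|---|---|
| 6 | 1.397·A | 0.427·A | 8.823·A |
| 12 | 1.195·A | 0.163·A | 4.105·A |
| 24 | 0.710·A | 0.043·A | 1.429·A |

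The maxima in a row need not fall at the same phase. At the worst phase for the 6-month gap, level is 1.205·A and slope 0.4232·A, so 1.205 + 18 × 0.4232 = 8.82. These figures place each month at its midpoint. Other ways of indexing the months move the level figure (about 1.2·A to 1.4·A on the two main ones) and the gap (8.6·A to 9.0·A), but not the slope.

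**Step 2: sizes for the 6 + 18 month model, worst phase.**

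| A | Level | Slope per month | Month-18 gap |
|---|---|---|---|
| 0.05 | 0.07 | 0.021 | 0.44 |
| 0.10 | 0.14 | 0.043 | 0.88 |
| 0.20 | 0.28 | 0.085 | 1.76 |

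At A = 0.10 the root mean square of the gap over phases is 0.62, and at some phases the gap is near zero. The sign reverses when the phase shifts by six months.

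**Step 3: patient-level simulation.** Quarterly visits, within-patient SD 0.6 (the protocol's figure), cluster-robust errors, a within-patient estimator standing in for the random intercept, no true effect, 300 runs per setting. At A = 0.10 and an unfavourable phase, the mean false month-18 gap is about ±0.9. The false-positive rate is 85–87% with 330 patients and 38–45% with 100. At a favourable phase the gap is about 0.1 and the rate is near nominal. With A = 0 the rate is 4–5%.

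**Step 4: effect of the remedies.** Adding one annual sine/cosine pair removes the bias at every phase if the cycle is a stable sinusoid, even with 6 pre-months. The standard error of the month-18 gap, in units of the residual SD of one monthly mean, then rises from 5.06 to 5.86. With the pair and 12 pre-months it is 2.44; with the pair and 24 it is 1.08. Twelve months without the pair still leaves 4.1·A, or 0.41 at A = 0.10. The pair therefore deals with the bias, and the longer window mainly restores precision.

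**The case against.** **The month-18 gap is not a declared effect.** The protocol reports level change and slope change; the figure near 0.9 is built from the two. That stands, so the declared effects come first here: 0.12 to 0.14 for level and 0.043 per month for slope at A = 0.10. The slope bias does fall on a declared effect, and the outcome definition does run to the end of the 18 months. If the primary effect were instead read as a plain change from the baseline mean to the end of implementation, seasonal bias would be at most about 0.13 at that amplitude. The segmented specification does not support that as the main reading.

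**Seasonality is an outside premise.** No section says that HbA1c varies by season at these sites, gives an amplitude or names the start month. This also stands, and it limits severity and confidence. A reader might infer that the pre-trend will be mostly seasonal, or that the trial is bound to be wrong by nearly a point. The protocol supports neither. It supports only that the stated model has no protection if a cycle exists.

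**A seasonal term could be left to a fuller plan.** In general it could. Here, however, the article itself fixes the baseline window and lists the fixed effects, so the point concerns what is stated.

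**A reader might infer that 24 months is the natural primary window, since MNCLHD data already go back about 36 months (12 + 24, taking study and implementation start as the same).** But 24 months reaches exactly to the start of outreach at MNCLHD. Any gradual response to the new clinics could enter the pre-trend and be projected forward. The protocol handles that period separately, so 24 months belongs in a sensitivity analysis.

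**The Discussion already urges caution about causal attribution.** That caution is general. It does not mention season and does not correct the estimate.

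**Conclusion.** The concern holds in conditional form. As specified, the primary model cannot distinguish a seasonal swing during the 6-month baseline from usual-care trend, and it projects whatever it finds over 18 months. Under an assumed sinusoid of amplitude 0.1 points, the worst-phase bias is about 0.12 to 0.14 in level change and 0.043 per month in slope change. These imply up to about 0.9 points at month 18, with a range of 0.44 to 1.76 for amplitudes of 0.05 to 0.2. The direction depends on both the start month and the timing of the seasonal peak, and at some phases the month-18 gap almost vanishes. The size rests on an amplitude, a sinusoidal shape and a phase that the protocol does not supply. This is a should-fix point with moderate confidence.

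**What to change.** 1. Add an annual sine/cosine pair to the primary model. Calendar-month terms are the alternative if the cycle may not be sinusoidal; they use more parameters.
2. Extend the retrospective HbA1c baseline from the electronic records to 12 months at all three sites. This covers a full annual cycle and matches the look-back already used for hospitalizations and screening.
3. Keep the 6-month window as one sensitivity analysis and a 24-month window as another, noting that the latter may carry the response to outreach at MNCLHD.

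The cost is small. MNCLHD HbA1c for these months is already to be collected, so the extra work is a longer record pull at NBMLHD. The protocol does not say how far back those records can be retrieved or what look-back the written consent covers, so both need checking. The sine/cosine pair adds two model terms. Recently diagnosed patients contribute less to the longer baseline, and the pre-trend must be roughly linear over 12 months instead of 6.
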